### Readiness for return to work scale

RTW after long-term sickness absence may be seen as a behavioural change or a process in several stages [40], depending on factors of which the person’s own RTW perceptions are predictive of future work participation [41–43]. The Readiness for RTW (R-RTW) scale [40] is based on the original stages of change model [44], which have been applied to various behaviours and across diverse disorders [45].

The R-RTW model addresses the motivational and social factors contributing to RTW behaviour and maintenance of work participation [46]. According to this model, the person progresses through stages of behaviour change i.e. RTW after sickness absence, shifting from the intention not to engage in RTW behaviour in the foreseeable future to a stage with initiating behaviour change, to maintain behaviour change and to RTW in a sustainable fashion.

Based on the score of the R-RTW scale it is possible to identify a person’s stage of readiness for change with regard to RTW allowing professionals, e.g. job consultants to tailor effective and individual support.

### Aim and hypotheses

The objectives are to apply an early, individually tailored occupational rehabilitation intervention to cancer survivors in two municipalities parallel with cancer treatment focusing on enhancing the R-RTW.

Two hypothesises;this early intervention conducted by a municipal job consultant will enhance the readiness for RTW and thereby increase the chance of RTW among cancer survivors from two municipalities compared with cancer survivors from municipalities not receiving this intervention but treated at the same hospital and receiving the standard municipal sick leave management.that socioeconomic status and/or co-morbidity will modify the effect of the intervention on RTW.

## Methods/Design

### Trial design

The study is a controlled trial conducted on cancer survivors treated at the Oncology Department, Aarhus University Hospital, Denmark with a 12 months follow-up.

### Participants

#### Intervention group

Cancer patients diagnosed with breast, colon-rectal, head and neck, thyroid gland, testicular, ovarian or cervix cancer referred to surgery, radiotherapy or chemotherapy at the Oncology Department at Aarhus University Hospital. Patients must be residents in the municipalities of Silkeborg or Randers, be at the age of 18–60 years and have a permanent or temporary employment (with at least 6 months left of their contract) at the inclusion date. Patients are eligible for participation whether they are still working or being on sick leave.

Patients, for whom the treating physician considers occupational rehabilitation to be unethical, or who are not reading or talking Danish are excluded.

Recruitment started in December 2013 and continues until the required sample size is obtained.

#### Control group

The control group is defined by patients with identical inclusion and exclusion criteria as the intervention group except that they live in other municipalities than Silkeborg and Randers.

The control group is identified via the electronic patient records at the Aarhus University Hospital.

### Recruitment of the intervention group participants

Patients are recruited to the intervention group in a three-stage process:At each cancer ward a nurse or assistant nurse assigned to this project identifies patients living in Randers or Silkeborg municipality with the eligible cancer diagnosis.The treating oncologist is notified of this patient and at first given consultation the patient is informed about the project, is handed a written information sheet also containing an informed written consent formula. The patient is asked to read the information sheet and is informed that a municipal job consultant will contact the patient at home by phone.The municipal job consultant may also identify eligible patients even before cancer treatment has begun because of sick leave spells exceeding 8 weeks. In that case the treating hospital ward is notified about inclusion status; in that way no cancer survivor is asked twice about inclusion.Finally the patient is telephoned by the municipal job consultant, who thoroughly informs the patient about the project. Participation includes the patients’ willingness to involve next of kin, employer, and colleagues. If the patient accepts participation the first meeting is set up and the informed written consent formula is signed on that occasion.

### Intervention

#### Control group

Cancer survivors in the control group will receive the usual municipal sickness benefit management within their municipal of residence as described in the background.

#### Intervention group

In both intervention municipalities the two job consultants attended a 4-days course in which they were specially trained by a psychologist in using elements of the Acceptance and Commitment Therapy (ACT) [23, 47] and the Individual Placement and Support Model (IPS) [48, 49].

During the inclusion- and intervention period the job consultants receive supervision by this psychologist once every month to secure a high degree of compliance with the intervention protocol.

#### Acceptance commitment and therapy

ACT is a development of cognitive behaviour therapy, which is based on recognition of the person’s values and immediate needs in current life situation. The goal of ACT is to increase psychological flexibility, which can be defined as the ability to contact the present moment more fully as a conscious human being, and to change or persist in behaviour that support one’s own values. Psychological flexibility is established through six core ACT processes: acceptance, cognitive fusion, being present, self as context, values, and committed action. Each of these areas is conceptualized as a positive psychological skill. The survivors are through dialogue with the job consultant confronted with these six core elements in order to enhance commitment and change in behaviour towards RTW [23].

#### Individual placement and support

The IPS inspired the way the job consultants systematize the actions by which they support RTW. The model originates from helping people with severe psychiatric illness to engage in paid employment, and builds on the following key elements: integration at the workplace, paid work, individualized services, and an ongoing individualised support [48, 49]. In this intervention the individualised support is “operationalised” in a number of phases, which correspond to the R-RTW obtained stages of change, i.e. a set of IPS-inspired actions are initiated according to the defined stage in which the survivor perceives him-/herself to be in: Pre-contemplation, Contemplation, Preparation for action - self-evaluative, Prepared for action – behavioural, Uncertain maintenance, or Proactive maintenance.

### Assessment of occupational rehabilitation needs

At the first meeting with the job consultant the cancer survivor is asked to answer an online questionnaire. The questionnaire data is used to guide the job consultant regarding the cancer survivor’s readiness for RTW and need of support in order to set up an individual RTW plan. Hence, the ACT inspired dialogue and the systematic occupational needs assessment are integrated in the IPS phases by which the job consultant supports the survivor’s RTW-process (Fig. 1). The job consultant sets up meetings with the cancer survivor according to the RTW plan. Throughout the intervention the rehabilitation plan is adjusted to the survivors’ needs, actual resources and readiness for RTW. The initial rehabilitation plan and the subsequent actions and adjustments are registered online alongside the questionnaire data by the job consultants.

**Fig. 1 Fig1:**
[figure not shown]
The structure used by the job consultants to tailor and support the return to work process. The individual rehabilitation plan is tailored according to different stages of readiness for return to work (R-RTW) and corresponding individual placement and support (IPS) actions that the job consultant initiates accompanied by acceptance and commitment therapy (ACT) inspired dialogue that should enhance commitment and change behaviour towards return to work (RTW)

The intervention continues for a maximum of one year or until RTW. The survivor answers the Readiness for RTW scale after three months and at one-year follow up.

### Online questionnaire

#### Co-morbidity

Eighteen co-morbidity questions asking whether the respondent suffer from or has suffered from (asthma, allergies, diabetes, hypertension, coronary thrombosis, angina, cerebral thrombosis, chronic obstructive pulmonary disease, osteoarthritis, rheumatoid arthritis, osteoporosis, cancer, migraine, minor psychiatric disorder, major psychiatric disorder, herniated disc or other back disorders, cataract, tinnitus). There are four response categories (no/never, yes/present, yes/previously, if previously yes - do you have any late complications?). Number of co-morbidities are counted if present or previously present and give late complications [50, 51].

#### Work intention

One question about intention to work (i) in your estimation, what are the chances that you will be able to work in six months?” measured with a 10-point rating scale ranging from 1 (no chance) to 10 (very large chance) [52].

#### Self-efficacy

The seven-item general self-efficacy scale from The Copenhagen Psychosocial Questionnaire (COPSOQ) (i) I can always manage to solve difficult problems if I try hard enough, (ii) if someone opposes me, I can find the ways and means to get what I want, (iii) I am certain that I can accomplish my goals, (iv) thanks to my resourcefulness, I can handle unforeseen situations, (v) I can remain calm when facing difficulties because I can rely on my coping abilities, (vi) when I am confronted with a problem, I can find several solutions, (vii) I can handle whatever comes my way. The response categories are (not at all true, barely true, moderately true, and exactly true) which were scored from 0–100 with 100 representing the highest degree of self-efficacy [53].

#### Social support

From the 2nd version of COPSOQ, three items about social support from colleagues and supervisors, respectively; (i) how often do you get help and support from your colleagues?, (ii) how often are your colleagues willing to listen to your problems at work?, (iii) how often do your colleagues talk with you about how well you carry out your work? and (i) how often is your nearest superior willing to listen to your problems at work?, (ii) how often do you get help and support from your nearest superior?, (iii) how often does your nearest superior talk with you about how well you carry out your work?. The response categories are (always; often; sometimes; seldom; never/hardly ever; not relevant, which are scored from 0–100 with 100 representing the highest degree of support [54].

#### Readiness for RTW

Finally, the Readiness for RTW will be measured by the Danish version of the original R-RTW scale [40]. The instrument consists of two scales; 22 items for persons not yet returned to work: (i) you do not think you will ever be able to go back to work?, (ii) you have been making plans with someone from your workplace to return back to work?, (iii) you have been thinking about making some changes that will help you go back to work?, (iv) as far as you are concerned there is no point in thinking about returning to work?, (v) you have learned different ways to cope with your pain so you can return to work?, (vi) you are actively doing things now to get back to work?, (vii) you think you might be ready to go back to work?, (viii) you are planning to go back to work, even if your pain is not 100 % gone?, (ix) physically, you are starting to feel ready to go back to work?, (x) you have been increasing your activities at home in order to build up your strength to go back to work?, (xi) you are getting help from others to return to work?, (xii) you are not ready to go back to work?, (xiii) you have found strategies to make your work manageable so you can return to work?, (xiv) mentally, you are starting to feel ready to go back to work?, (xv) you have been wondering if there is something you could do to return to work?, (xvi) you worry about having to stop working again due to your injury?, (xvii) you have started thinking about going back to work”?, (xviii) you have a date for your first day back at work?, (xix) you wonder if you will be able to go back to work?, (xx) you wish you had more ideas about how to get back to work?, (xxi) you would like to have some advice about how to go back to work?, (xxii) as far as you are concerned, you do not need to go back to work ever”?.

And a scale with 12 items for those who have returned to work (part-time or full-time), but are at risk of sickness absence relapse: (i) you are trying different strategies to stay at work?, (ii) you are doing everything you can to stay at work?, (iii) you are getting help from others to stay at work?, (iv) you are working hard to find ways to cope with the difficulties of being back at work?, (v) you have learned different ways to cope with your pain so that you can stay at work?, (vi) you are taking steps to prevent having to go off job again due to your injury?, (vii) you have found strategies to make your work manageable so you can stay at work?, (viii) you are back at work but are not sure you can keep up the effort?, (ix) you worry about having to stop working again due to your injury?, (x) you still find yourself struggling to stay at work due to the effects of your injury?, (xi) you are back at work and it is going well?, (xii) you feel you may need help in order to stay at work?. Each item is scored on a five point ordinal scale (1 = strongly disagree) to (5 = strongly agree). Mean scores are calculated and forms four underlying stages for those not returned to work: Precontemplation, Contemplation, Preparation for action - self-evaluative, and Prepared for action - behavioural. And two stages for those already returned to work: Uncertain maintenance and proactive maintenance. The stage obtaining the highest mean score is interpreted as the current stage of readiness. The score of the R-RTW scale is immediately calculated in the online questionnaire. Measurements will be repeated after three and twelve months.

### Outcomes

#### Primary

The primary outcome is RTW among cancer survivors in the intervention group compared with the control group.

RTW is defined by at least 4 consecutive weeks of no social transfer payments or attending a modified job called “flexi job”.

The outcome is identified in a national register on weekly public transfer payments called the Danish Register for Evaluation of Marginalisation (DREAM) which has been found to provide valid information on labour market outcomes [55, 56]. Four consecutive weeks of no social transfer payments are considered to be equivalent to RTW along with four consecutive weeks of transfer payment equivalent to attending a “flexi job”.

#### Secondary

The secondary outcomes are whether socioeconomic status or co-morbidity is modifying the effect of the intervention on RTW.

Socioeconomic status is defined by type of work, educational level and last year household income before taxes, which are collected from Statistics Denmark [57].

Co-morbidity is defined by the Charlson-index; a weighted index including the number and seriousness of co-morbid diseases [58]. Data on diagnosis used in the Charlson-index are collected from the National Patient Registry in Denmark [59].

### Sample size calculation

The sample size calculation is based on the primary outcome RTW.

Approximately 450 patients are annually referred to the oncology ward with the eligible cancer diagnosis of which 20 % reside in the two intervention municipalities. It is expected that the employment rate among cancer patients would correspond to that of the Danish background population equivalent to approximately 80 % [60]. Furthermore, it was anticipated that 80 % gave informed consent to participate in the study. Hence, an expected number of 288 cancer patients per year. We estimated a mortality rate of 10 % during the one-year follow-up. Based on previous studies the RTW rate among cancer survivors who underwent occupational rehabilitation is approximately 82 % [18], and that the share will be approximately 60 % in the control group [61, 62]. The hazard ratio (HR) is then given by: (HR: ln (40 %) / ln (18 %) = 1.87). With a power of 90 % and a significance level of 5 % a required sample size of 290 patients is needed. To obtain sufficient strength in the adjusted analyzes 250 survivors should RTW. Thus, the total number of cancer survivors required is 430 (of which 90 reside in the two intervention municipalities) which means an inclusion period of 1.5 years.

### Statistical analyses

#### Primary outcome

The cumulative incidence proportion (CIP) as a function of the number of follow-up weeks is estimated using the Kaplan-Meier curve. The relative cumulative incidence of RTW within 52 weeks will be analyzed in a generalised linear regression model using the pseudo values method [63, 64].

Entry time is defined as the end of cancer treatment (identified from the hospital records) and the end of follow-up is 52 weeks following entry time. The outcome variable RTW consists of two measures: an event indicator (yes or no) and the time until RTW is identified in the DREAM register [65] or end of follow-up / competing risks (*early retirement benefit, retirement pension or death*)/censored observations (*emigration*), whichever comes first.

Adjustments for gender, age, cancer diagnosis, time since diagnosis and Charlson’s co-morbidity index [58] are going to be carried out. Moreover, analyses of whether socio-economic status or Charlson’s co-morbidity index modifies the effect of the intervention on RTW will also be carried out.

The significance level is set at p < 0.05. The results will be shown as crude and adjusted relative cumulative incidences, i.e. risks (RR) and corresponding 95 % confidence intervals (95 % CI).

STATA version 13.1 will be used as statistical software.

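### The cumulative incidence of return to work is to be estimated by Kaplan-Meier although the plan names competing risks, so the reported proportions will be too high by about 3 percentage points at the plan's own mortality

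*Protocol article*

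**What the plan says.** All but one of the relevant statements stand in the Protocol article, Statistical analyses, Primary outcome.

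- Curve: "The cumulative incidence proportion (CIP) as a function of the number of follow-up weeks is estimated using the Kaplan-Meier curve".
- Comparison: "The relative cumulative incidence of RTW within 52 weeks will be analyzed in a generalised linear regression model using the pseudo values method". The estimator from which the pseudo values are formed is not named.
- Event coding: "The outcome variable RTW consists of two measures: an event indicator (yes or no"), together with the time to RTW or to the end of observation.
- End of observation: "the end of follow-up is 52 weeks following entry time", or earlier at "competing risks (*early retirement benefit, retirement pension or death*)/censored observations (*emigration*), whichever comes first".

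The Sample size calculation adds: "We estimated a mortality rate of 10 % during the one-year follow-up". This is one figure, not split by group, and no figure is given for retirement. The same section expects RTW of 82% with the intervention and 60% without.

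**The concern.** The plan separates competing events from censoring and then names an estimator that cannot keep them apart. Once time stops at death or retirement and the indicator has only two values, Kaplan-Meier handles a patient who died exactly as it handles one who emigrated. It removes the patient from the risk set and assumes that RTW would have followed at the rate seen in those who remain.

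The result estimates RTW in a hypothetical population in which nobody dies or retires. It is never below the actual cumulative incidence, and it lies above it as soon as one competing event comes before a later RTW. The primary result is expressed in cumulative incidences, so the published RTW percentages are affected directly. The RR would be affected too if the pseudo values came from the same estimator.

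**Working it through.** **Inputs from the Sample size calculation.** RTW 60% (control) and 82% (intervention); mortality 10% in the follow-up year; hazard ratio 1.87; power 90%; significance level 5%; 20% of patients from the intervention municipalities.

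**Assumptions added here.** Constant, independent hazards over the 52 weeks; the same mortality hazard in both groups, before and after RTW; no retirement.

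**The plan's own figure first.** Schoenfeld events, two-sided: (1.960 + 1.282)² / (0.2 × 0.8 × (ln 1.87)²) = 167.6, so 168. Share with RTW: 0.2 × 0.82 + 0.8 × 0.60 = 0.644. 168 / 0.644 = 260.9, and 260.9 / 0.90 = 289.9. This is the stated 290, so the 10% mortality entered the sizing as a loss of patients.

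**Formulae.** With RTW hazard L and competing hazard M per year:

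- 1-KM = 1 − exp(−L)
- cumulative incidence (CIF) = L / (L + M) × (1 − exp(−(L + M)))

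Ten per cent one-year mortality gives M = −ln 0.90 = 0.1054.

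**Main calculation: 60% and 82% are the true cumulative incidences.** Solve CIF = 0.60 and CIF = 0.82 for L.

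| True RTW | L | 1-KM | Excess |
|---|---|---|---|
| 60% | 0.986 | 62.7% | 2.7 points |
| 82% | 1.901 | 85.1% | 3.1 points |

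RR from 1-KM: 0.851 / 0.627 = 1.357. True RR: 0.82 / 0.60 = 1.367.

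**Alternative reading: 60% and 82% are already 1-KM values.** The plan's hazard ratio treats them so, since 1.87 is ln 0.18 / ln 0.40. Then L = 0.916 and 1.715, and the CIFs are 57.4% and 78.9%. The excess is 2.6 and 3.1 points. RR 1.367 (1-KM) against 1.375 (CIF).

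**Range for the competing risk** (an assumption, since the plan gives no retirement figure). In the main calculation, an equal one-year competing risk of 5% gives an excess of 1.3 and 1.5 points, and 20% gives 5.7 and 6.2 points (60% and 82% groups).

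**A larger figure, and why it is not used.** If 10% of each group had a competing event before RTW, the total hazard is −ln(1 − 0.60 − 0.10) = 1.204, split 6:1, and 1-KM is 64.4%. At 82% the total is −ln(0.08) = 2.526, split 82:10, and 1-KM is 89.5%. The excess is 4.4 and 7.5 points and the RR is 1.390. The competing hazards are then 0.172 and 0.275, which means one-year mortality of 1 − exp(−0.172) = 16% and 1 − exp(−0.275) = 24%. The plan says 10% for all deaths, including those after RTW.

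**Unequal competing risk** (illustrative, 5% in one group and 10% in the other). Across the readings above, the RR from 1-KM and the RR from the CIF differ by about 0.02 to 0.08. For example, on the alternative reading with 5% intervention and 10% control, the CIF ratio is 1.402 against 1.367.

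**The case against.** The strongest reply is that the Kaplan-Meier sentence concerns only the curve over follow-up weeks, while the reported RR comes from a separate step. Pseudo values can be formed from the cumulative incidence function, and listing competing risks apart from emigration fits that choice. An article may also leave this specification to a fuller document. This stands as far as the RR is concerned: the yes/no indicator points the other way, so the text is ambiguous.

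A reader might go further and infer that the primary RR is biased, or that any difference in mortality between municipalities becomes a spurious RTW effect. The documents do not support that.

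- The estimator behind the pseudo values is not stated. A complaint that the censoring would depend on diagnosis, and so break the method's assumption, rests on the same open point.
- Under independent constant hazards the 1-KM ratio does not change with mortality; the CIF ratio does. With 1-KM at 60% in both groups and mortality of 15% against 5%, the 1-KM ratio is 1.00, while the CIF ratio is 0.561 / 0.587 = 0.96. The two ratios answer different questions.
- No group-specific mortality or retirement is given. All patients are treated at one hospital under otherwise identical criteria, with adjustment for age, diagnosis and comorbidity among others. A large imbalance is possible without randomisation, but nothing in the document indicates one.

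It could also be said that Kaplan-Meier gives the right proportion if patients with a competing event stay in the risk set to week 52. The plan rules this out by ending their time at the event. None of these replies rescues the sentence about the curve.

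**Conclusion.** The point holds for the cumulative incidence proportion. The stated estimator conflicts with the stated event structure, and the direction of the error is certain. At the plan's 10% one-year mortality the overstatement is about 2.7 points at a true RTW of 60% and 3.1 points at 82%, assuming constant hazards, equal mortality in both groups and no retirement. Retirement would raise it by an amount the document does not allow one to fix.

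For the RR, only an ambiguity is shown. Had the pseudo values been built from Kaplan-Meier, the RR would shift by about 0.01 to 0.02 with equal competing risks. It is slightly low on the two readings that use 10% total mortality, and slightly high if 10% is the proportion with a competing event before RTW. Only a difference in competing risk between the groups would move it further. This is a wording fault worth correcting before analysis, and it does not show that the primary comparison is invalid. It should be settled in advance, because the Methodological considerations state that the analyst will not be blinded.

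**What to change.** Replace the Kaplan-Meier sentence and the event definition so that the section states three things:

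1. The cumulative incidence proportion is estimated with the Aalen-Johansen cumulative incidence function.
2. The event variable has three levels: RTW; competing event (death, early retirement benefit or retirement pension); censored (emigration or end of follow-up).
3. The pseudo values at 52 weeks are computed from that same estimator.

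The cost is a few lines of text and a different pseudo-value calculation on data already to be collected. The sample size need not change for this reason, since its derivation already divides by 0.90 for mortality. The one visible consequence is that the reported RTW percentages will be slightly lower than Kaplan-Meier would show.

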### Methodological considerations

The golden standard when effects of an intervention are to be assessed is the randomised controlled trial (RCT) [18]. However, when studies are conducted in real settings, like in municipal job centres; recently published articles from the Danish national return-to-work program showed challenges in applying a randomised study design; i.e. spill over effects between study arms within the municipality [67–69]. Therefore we chose a controlled study design. When the control municipalities are to be chosen, high priority will be given to municipalities that resemble the RTW rate of the intervention municipalities the year before our study was initiated, i.e. 2013. For that purpose official rates from Statistics Denmark [57] will be used. We may not be able to identify municipalities which also can supply sufficient numbers of cancer patients fulfilling the inclusion and exclusion criteria. We might need to compromise on which municipalities to include as controls to get sufficient numbers of cancer survivors, which in turn might give residual confounding that will lower the internal validity of our results.

We believe that if the job consultants are to succeed in their support and help to the cancer survivors and thereby increase the R-RTW; they must identify barriers and facilitators in the RTW process and use the ACT inspired dialogue. Otherwise they may not be able to engage the cancer survivors in committed actions that are value-based and make sense to the survivors’ perception of quality of life (including work). In order for us to keep track of the compliance with the study protocol; the job consultants attend monthly supervisions with the psychologist who trained them in the use of ACT and IPS. Because the intervention takes place in the job consultants usual work setting, we fear that they are at risk of resuming old work habits and thereby violate the innovative elements in our intervention. We anticipate that the supervisions act as an arena where experiences are shared and difficult situations are discussed in order for the job consultants to learn and cope with their new job tasks and demands.

Due to the described intervention given by the job consultants it is not possible to blind the cancer survivors nor the job consultants or the person who will perform the analyses.

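### The intervention is allocated by whole municipality, but the sample size assumes independent patients and the stated primary model has no municipality component

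*Protocol article*

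**What the plan says.** Allocation is by place of residence. In the participants section, "Patients must be residents in the municipalities of Silkeborg or Randers, be at the age of 18–60 years". The control group meets the same criteria "except that they live in other municipalities than Silkeborg and Randers", and its number of municipalities is not fixed. Delivery is also concentrated: "In both intervention municipalities the two job consultants attended a 4-days course".

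Methodological considerations explains why patients were not randomised, citing "spill over effects between study arms within the municipality". The same section gives priority to control municipalities whose 2013 RTW rate resembles that of the intervention municipalities.

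The sample size section states: "With a power of 90 % and a significance level of 5 % a required sample size of 290 patients is needed". It then raises the total to 430, of whom 90 live in the intervention municipalities, so that 250 RTW events are available for the adjusted analyses. It mentions no ICC, design effect or number of control municipalities.

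The statistical analyses section says the 52-week relative cumulative incidence "will be analyzed in a generalised linear regression model using the pseudo values method". Adjustment is for gender, age, cancer diagnosis, time since diagnosis and Charlson index, with p < 0.05 and a 95% CI. Municipality does not appear, and no variance estimator is named.

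**The concern.** When everyone in a municipality receives the same arm, a difference between job centres or local labour markets cannot be separated from the intervention by adding patients. It can only be judged against the variation between municipalities, and there are just two on the intervention side. The protocol accepts that RTW rates differ between municipalities, since it wants to choose controls on that rate. If the analysis treats patients as independent, ordinary variation between municipalities enters the estimate but not its standard error. The primary p-value and CI then err in the anti-conservative direction, and the stated power is higher than the design delivers.

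**Working it through.** **Inputs from the sample size section.** RTW 82% (intervention) and 60% (control); HR 1.87; 5% significance, 90% power; 20% of patients in the intervention municipalities; 10% mortality; totals 290 and 430 (90 intervention, 340 control). The ratio printed for the HR, ln 0.40 / ln 0.18, equals 0.534; its inverse is 1.87, and 1.87 is the value used.

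**Assumed, because the article gives neither.** ICC 0.01 to 0.02, which at a 60% RTW rate is a between-municipality SD of √(0.01 × 0.24) = 4.9 to √(0.02 × 0.24) = 6.9 percentage points; K = 8 equal-sized control municipalities. Other values follow below.

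**1. Reproduce 290.** Schoenfeld events = (1.960 + 1.282)² / (0.20 × 0.80 × (ln 1.87)²) = 168. Event probability = 0.2 × 0.82 + 0.8 × 0.60 = 0.644. Then 168 / 0.644 / 0.9 = 289.9, that is 290, with power 90.1%. There is no reserve and no room for a design effect. The 430 also reproduces: 250 / 0.646 / 0.9 = 430, where 0.646 is the event probability with 90 of 430 in the intervention arm. That step is for covariate adjustment, not for clustering.

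**2. Add clustering.** With d events and intervention share a, the independence variance of ln HR is 1/(d·a) + 1/(d·(1 − a)). Multiply each arm's term by D = 1 + (m − 1) × ICC, where m is the number analysed per municipality. This is an approximation. Power = Φ(ln 1.87 / SE − 1.96). True type I error of the unclustered test = 2 × (1 − Φ(1.96 / r)), where r is the ratio of the true SE to the independence SE.

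*At 430:* 81 and 306 analysed, so m = 81/2 = 40.5 and 306/8 = 38.25; d = 250; a = 90/430. The independence variance is 0.01911 + 0.00506 = 0.02417.
- ICC 0.01: D = 1.395 and 1.373; variance 0.0336; r = 1.18; power Φ(3.415 − 1.96) = 93%; type I error 9.6%.
- ICC 0.02: D = 1.790 and 1.745; variance 0.0430; r = 1.33; power Φ(3.017 − 1.96) = 85%; type I error 14.2%.
- With a at exactly 20% in place of 90/430, power is 92% and 85%.

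*At 290:* m = 26.1 in both arms; independence variance 0.0372.
- ICC 0.01: D = 1.251; variance 0.0465; r = 1.12; power Φ(2.902 − 1.96) = 83%; type I error 8.0%.
- ICC 0.02: D = 1.502; variance 0.0559; r = 1.23; power Φ(2.649 − 1.96) = 75%; type I error 11.0%.

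Using 82% against 60% as two proportions, closer to the planned risk ratio, gives the same SE ratios at 430 (1.18 and 1.33).

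**3. Small-sample reference.** With 2 + K municipalities, a municipality-level comparison has K degrees of freedom. Power for K = 8, same variances:

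| N | ICC | Normal | t, 8 df |
|---|---|---|---|
| 290 | 0 | 90% | 81% |
| 290 | 0.01 | 83% | 72% |
| 290 | 0.02 | 75% | 64% |
| 430 | 0 | 98% | 94% |
| 430 | 0.01 | 93% | 85% |
| 430 | 0.02 | 85% | 75% |

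**4. Sensitivity.** For K = 4 to 16 (normal reference), power at 290 is 81 to 84% at ICC 0.01 and 73 to 77% at 0.02. At 430, power falls below 90% once the ICC exceeds about 0.012 (K = 4) to 0.015 (K = 16). At ICC 0.005 and K = 8, power is 86% at 290 and 96% at 430, and type I error at 430 is 7.3%.

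**The case against.** Five points on the other side carry weight.

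- *The article does not say that patients are independent.* This is right for the analysis. A reader might infer that the plan commits to independence standard errors, but the statistical analyses section names no variance estimator, and an unseen analysis plan could supply a clustered one. The statement about the CI is therefore conditional on the analysis being run as written. The sample size does not share this escape, because the printed 290 leaves no room for a design effect.
- *The trial will enrol 430 or more, not 290.* This also stands. A reader might infer that the trial is underpowered, but at 430 that depends on the ICC. The extra patients do not protect type I error, however: more patients per municipality raise the SE ratio (1.12 at 290, 1.18 at 430, ICC 0.01).
- *The ICC and K are assumed.* They are, and choosing controls with similar 2013 RTW rates could reduce the variation. The direction holds for any ICC above zero; the size does not. Nor does the article say that control municipalities manage sickness benefit differently. It says only that each applies its usual management.
- *Two tempting overstatements fail.* Municipality variation is not the dominant source of uncertainty in these scenarios: at 430 it is 1 − 1/1.179² = 28% to 1 − 1/1.334² = 44% of the variance. Nor should a t-based power be set against the stated 90% and the whole gap put down to clustering, since t on 8 df gives 81% at 290 even with ICC 0.
- *The protocol already admits a limitation.* Methodological considerations admits residual confounding from compromises over controls. That is bias; it does not address the width of the interval.

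**Conclusion.** The point holds for the sample size without reservation: 290 delivers 90% power only if RTW does not vary between municipalities, and neither 290 nor 430 contains an allowance for such variation. It holds for the analysis conditionally: run with the listed patient-level covariates and no municipality component, the primary CI would be too narrow and the test anti-conservative. With ICC 0.01 to 0.02 and 8 control municipalities, both assumed, type I error at 430 is about 10 to 14% instead of 5%. On the Schoenfeld basis with a normal reference, power loses about 7 to 15 points at 290 and about 5 to 13 points at 430. A small-sample reference lowers it further. The documents do not support a firm statement that the trial as planned falls below 90% power.

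**What to change.** In the statistical analyses section, base the primary p-value and CI on a method that accounts for municipality and uses small-sample degrees of freedom. Two options are covariate-adjusted mean pseudo-values per municipality, compared 2 against K with t on K degrees of freedom, or a random municipality effect with a small-sample correction. Do not rely on a plain sandwich estimator, which is unreliable with two treated clusters. A permutation test over which two municipalities carry the intervention label is usable only if K is large enough: with K = 4 there are 15 arrangements and the smallest p is 1/15 = 0.067, while K = 5 gives 1/21 = 0.048.

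In the sample size section, state that 290 and 430 assume no variation between municipalities, give power over a range of ICC and of K, and state the limit set by having only two intervention municipalities.

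The cost is a few lines of text, wider intervals and a lower stated power; no extra patients are required if that lower power is accepted openly. Adding control municipalities improves precision but is not free: Methodological considerations already warns that widening the choice may cost comparability, so the two must be weighed.
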